#### Outcome measures

##### Primary outcome measure

The primary outcome measure (Table 2, Fig. 1) is the degree of decisional conflict, a central determinant of decision making, which is defined as ‘personal uncertainty about which option to choose’ [38]. This will be measured with the translated Decisional Conflict Scale (DCS). The DCS is a self-report questionnaire comprising sixteen questions about personal perceptions of: a) uncertainty in choosing options, b) modifiable factors contributing to uncertainty such as feeling uninformed about alternatives, benefits and risks, unclarity about personal values and unsupported in decision making, c) effective decision making such as feeling the choice is informed, values-based, likely to be implemented and expressing satisfaction with the choice [39]. Each item is measured on a 5-point Likert scale (0 = strongly agree to 4 = strongly disagree). Besides the total score, the DCS has the following five sub scores: certainty, information, clarification of values, support or pressure from others and the patient’s perception of the quality of the decision process. To calculate the total and sub scores the item scores will be summed, divided by the number of items and multiplied by 25. The scores thus range from 0 (no decisional conflict) to 100 (extremely high decisional conflict). By appropriate application of SDM using ROM, decisional conflict is expected to be lowered. Individuals whose scores will be higher than 37.5, are considered to be uncomfortable with the decision and tend to delay it. Scores lower than 25 will be associated with absence of decisional conflict. In this study we will examine whether the total and sub scores at this scale are associated with the implementation of the SDM-ROM model [38, 39].

**Table 2 Tab2:** Primary and secondary outcome parameters

Topic & Instrument	Method	Patient	Patient	Patient	Clinician	Organisation
		T0	T1	T2		
Primary Outcome Parameter						
Patient’s perception of SDM						
Patient						
Decisional Conflict Scale	SR	X	X	X		
Secondary Outcome Parameter						
Patient-clinician relationship						
Patient						
Working Alliance Inventory	SR	X	X	X		
Clinician						
Working Alliance Inventory (patient level)	SR				X (T2)	
Additional outcome measures						
Compliance						
Organization						
Drop out (patient level)	EPR					X (T2)
No-Show (patient level)	EPR					X (T2)
Symptoms-functioning						
Patient						
OQ-45	SR	X	X	X		
Quality of life						
Patient						
MANSA-16	SR	X	X	X		

*SR* self-report, *EPR* Electronical Patient Record

T0 = baseline

T1 = Follow-up +/−3 months after baseline (between 10 and 16 weeks)

T2 = +/−6 months after baseline (between 23 and 29 weeks)

**Fig. 1 Fig1:**
[figure not shown]
Primary and secondary outcome parameters in flow chart

The psychometric properties of the scale are acceptable. Test-retest correlations and Cronbach alpha coefficients exceed 0.78 (reliability). The scale correlates to related constructs (knowledge, regret, discontinuance) and discriminates between groups who make and delay decisions (construct validity). DCS is responsive to change between different decision supporting interventions. Effect sizes range from 0.4 to 1.2 for the total scale. The predictive validity of the DCS is also demonstrated. Finally, the instrument is easy to administer [38].

Application of the revised Dutch DCS is not known to us. For this study the DCS is translated from English into Dutch by two translators separately, who subsequently established a consensus version. The consensus version was back translated into English by one independent native English translator. The native speaker and the research team checked and discussed the discrepancies between the original version and the translation, which resulted in a final Dutch version [40].

#### Secondary outcome measures

The secondary outcome measures (Table 2, Fig. 1) are the patient-clinician relationship, patient’s adherence to treatment, clinical outcome and quality of life. The patient-clinician relationship will be assessed using the Dutch version of the Working Alliance Inventory Short Form (WAI-S) [41–43]. For this study the WAI-S is chosen, because the questionnaire measures the quality of the alliance on the basis of three aspects related to SDM: contact/bond, agreement on goals and agreement on tasks [43–45]. Besides, the WAI-S has patient and clinician versions, which are both used in this study. The questionnaire consists of twelve questions concerning the agreement about treatment targets and tasks, and the interpersonal connection between patients and clinicians. The WAI-S scores from 1 (rarely or never) to 4 (always). Stinckens et al. [43] report a three factor structure of the patient version of the instrument: a contact/bond, a task and a goal component. Tracey et al. [41] also found evidence for one overall score. Psychometric qualities of the WAI-S proved to be good [41,43, 46, 47]. The scale correlates with outcome moderately. The perspective of the patient and a high score on the task scale are the strongest predictors for positive outcome [43].

In addition to these outcomes, the influence of the patients’ commitment to the treatment plan will be investigated. Data about no-show and drop out will be extracted from the electronic patient record by each team.

Finally, effects of SDM using ROM on treatment results will be studied with either the Manchester Short Quality of Live Measurement (MANSA-VN-16) [48] for long term patients or the Outcome Questionnaire (OQ-45) [49] for short term patients.

The MANSA-VN-16 is a self-report questionnaire which measures how satisfied the patient is in each of the following life domains: living situation, social relationships, physical health, mental health, safety, financial situation, work situation and life as a whole. Twelve questions are answered on a 7-point scale (1 = not satisfied, 7 = very satisfied) and four items are rated by ‘yes’ or ‘no’. An overall score of subjective quality of life can be calculated as a mean overall score. A higher score on the MANSA means a better quality of life. The psychometric properties are satisfactory [50].

De OQ-45 is a self-report scale with 45 items, which measures symptoms, emotional states, interpersonal relationships and social role functioning. Each item is measured on a 5-point Likert scale (0 = never to 4 = almost always). Scoring is reversed for nine positively formulated items. The scores of the items are summed. This means a total score ranging from 0 to 180. Higher scores reveal reporting of more frequent symptoms, distress, interpersonal problems and social dysfunction. Apart from the total scale, the Dutch OQ-45 has the following four subscales: symptomatic distress, anxiety and somatic distress, interpersonal relations, social role. Results show that the psychometric properties of the Dutch OQ were adequate and similar to the original instrument [51].

#### Treatment integrity

To check the treatment integrity in the intervention teams, one structure indicator will be measured and three process evaluation approaches will be conducted (Table 3). The structure indicator will report how frequently the primary ROM-instrument is completed. The process evaluation will indicate the implementation stage of the SDM-ROM model in the intervention teams.

**Table 3 Tab3:** Treatment integrity check and measuring moments

Topic & Instrument	Method	Patient	Patient	Patient	Clinician
		T0	T1	T2	
Treatment Integrity Check					
Patient					
SDM-Q-9	SR	X	X	X	
ROM-questions	SR	X	X	X	
Clinician					
SDM-Q-9 (patient level)	SR				X (T2)
ROM-questions (patient level)	SR				X (T2)
Survey about ROM in daily clinical practice. (clinician level)	SR				X (T0, T1, T2)

T0 = baseline

T1 = Follow-up +/−3 months after baseline (between 10 and 16 weeks)

T2 = +/−6 months after baseline (between 23 and 29 weeks)

Survey ROM in daily practice in intervention and control group

The following three process scales will be used:Four questions for patients and clinicians, developed by the research team, about the added value and use of ROM feedback in the conversation between patients and clinicians. Patients in the intervention group will be asked to fill out the four ROM-questions at T0, T1 and T2. At T2 clinicians will complete the same questions regarding the consultations with their patients.The SDM-steps will be measured with the translated Shared Decision Making-Questionnaire-9 (SDM-Q-9), which has a version for patients and one for clinicians. Both versions ask the patient and clinician first to enter the health problem the consultation was about and which decision was made. The questionnaire continues with nine items about the steps in the SDM process, scoring at a six point scale that ranges from 0 (completely disagree) to 5 (completely agree). A total score can be calculated by summing the scores of all items. A high score indicates more SDM. The SDM-Q-9 shows a high reliability. The available results about the factorial validity are also positive [51, 52]. The SDM-Q-9 versions were translated into Dutch by the research team conform the standards of forward and backward translations (ref. section primary outcome measure, [40]). A recent publication about psychometric testing of a translated Dutch version of the SDM-Q-9 [53] demonstrated good acceptance, internal consistency, and acceptable to good convergent validity of the versions for patients and physicians. Patients in the intervention group will be asked to complete the SDM-Q-9 at T0, T1 and T2. At T2 clinicians will complete the same questions regarding the consultations with their patients.A general survey for clinicians of the intervention and control group at three moments in a year about ROM in daily clinical practice [50]. The survey consists of one question about the extent of using ROM in daily practice, with five response categories from ‘never’ to ‘always’. If a clinician scores ‘never’, the first question is followed by an open question about the reason(s) of this. After scoring the other answers, 23 statements about the implementation of using ROM will be submitted. The statements have five response categories, ranging from ‘strongly disagree’ (score 1) to ‘strongly agree’ (score 5). A higher score means a better implementation of ROM in daily practice. The development of the survey is described in a paper of the Trimbos-institute, Netherlands Institute of Mental Health and Addiction [54].

#### Patients’ characteristics at baseline: moderator and potential covariates

At baseline the following characteristics of patients (Table 4) will be collected: socio-demographics (sex, age, and educational level), diagnosis, length of treatment and locus of control. Locus of control is measured with the Mastery Scale [55]. This scale is designed to measure the degree to which people perceive that they can control factors that influence their life situation. The scale has been widely used and translated into multiple languages. Because no standardized scoring recommendations were provided, investigators developed their own scoring protocols and the studies are difficult to compare. The original Pearlin Mastery Scale showed good construct, predictive validity and internal consistency. The Dutch version, used in the baseline measurement of this study, consists of five negatively worded items with five ordered response categories from 1 (strongly agree) to 5 (strongly disagree), where 5 indicates the highest level of self-mastery. A total score can be calculated by summing the scores of all items (range 5–25). This version is also used in NEMESIS-I, a Dutch study of mental and physical health and wellbeing. The reliability of this version is good [55].

**Table 4 Tab4:** Patients’ characteristics

Topic & Instrument	Method	Patient	Clinician	Organisation
		T0	T0	T0
Patients’ characteristics at baseline				
Patient				
Educational level	SR	X		
Locus of Control-Mastery	SR	X		
Organisation				
Age	EPR			X
Sex	EPR			X
Diagnosis	EPR			X
Care domain	EPR			X
Length of treatment	EPR			X

*SR* self-report, *EPR* Electronical Patient Record

### Sample size

This study is designed to detect a medium effect size of *d* = 0.5 on the primary outcome between the intervention and control group. A significance level set at α = 0.05 and 65 patients per arm yield a power of 0.80 [56]. Due to the cluster-randomisation at team level, we will calculate the effective sample size with an intra cluster correlation coefficient (ICC). The ICC is a measure of relatedness of responses within a cluster [57]. When adjusting for clustering within teams we expect an ICC = 0.05. Using the following formula [57]: Design Effect (DE) = 1 + (m-1) ICC (0.05), the sample size needs to be 136 patients per arm. Finally we expect a drop out of 25 %. This requires an initial inclusion of 182 patients per arm, which means that on average 31 patients per team per arm, will be included.

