## Methods/Design

### Trial design

The study is designed as a multi-centre two-arm cluster randomised controlled trial of Shared Decision Making (SDM) in specialised mental health care using Routine Outcome Monitoring (ROM) as a source of information. A cluster randomised design in which the unit of randomisation is the treatment team is deemed necessary to prevent spill-over effects between intervention and control groups. During recruitment of teams for the study, pairs of teams from the same mental health organisation are randomly assigned to either the experimental or control conditions (matched pairs). Control teams will implement the SDM and ROM model after the completion of the study.

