### Participants and setting

The study takes place in specialised mental health care organisations. Due to the expected generic applicability of the SDM-ROM model, the model is being tested to various subgroups with the following characteristics: age (adolescents, adults and elderly patients), diagnosis (psychotic, common mental and personality disorders) and setting (outpatient, day-clinic and clinic). In this study, a total of six intervention and six control teams from four organisations participate. In accordance to the sample size calculation (ref. section sample size) the teams will include 364 patients (182 in the intervention group and 182 in the control condition, with an average of 31 patients per team). Patients who don’t speak and read Dutch are excluded from the study.

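### The power of 0.80 is carried to a 12-team design by the design effect alone; on the plan's own inputs a team-level test on 10 degrees of freedom has about 0.73

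*Protocol article*

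**What the plan says.** The calculation is set out in the Sample size section of the protocol article. The trial is "designed to detect a medium effect size of" d = 0.5 on the primary outcome, and at a significance level of 0.05, "65 patients per arm yield a power of 0.80". Clustering comes in afterwards: "When adjusting for clustering within teams we expect an ICC = 0.05". With a design effect of 1 + (m − 1) × ICC, "the sample size needs to be 136 patients per arm". The last step is attrition: "Finally we expect a drop out of 25" per cent, and "This requires an initial inclusion of 182 patients per arm", or about 31 per team.

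The number of clusters is given under Participants and setting: "a total of six intervention and six control teams from four organisations participate". Trial design describes the allocation: "pairs of teams from the same mental health organisation are randomly assigned to either the experimental or control conditions (matched pairs"). Statistical analyses plans multi-level analyses and mentions neither the pairing nor a small-cluster reference distribution.

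**The concern.** Teams are randomised, so the treatment contrast lies between teams. Its error variance has to be estimated from 12 team-level values, which leaves 10 degrees of freedom, or 5 if the analysis is by matched pair. The design effect inflates the patient count so that the variance of the contrast matches that of about 65 independent patients per arm. It does not change the reference distribution. A power of 0.80 carried through that step is therefore a large-sample figure, in effect one for a trial with many teams.

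This is the only power justification for the primary outcome. If it is too favourable, readers will take the trial's sensitivity to d = 0.5 to be higher than 12 teams can give.

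**Working it through.** **Inputs.** From Sample size: d = 0.5 (SD 1 on the standardised scale), alpha 0.05, ICC 0.05, 136 analysed per arm, 25% dropout. From Participants and setting: six teams per arm. From Trial design: matched pairs, hence six pairs. The article does not say whether alpha is two-sided. Two-sided reproduces its figure (0.81) and one-sided does not (0.88), so two-sided is used.

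**Step 1: reproduce the plan's chain.**
- 65 per arm, individually randomised: noncentral t on 128 df gives power 0.808 (normal approximation 0.813). The stated 0.80 holds.
- Design effect with m = 23: 1 + 22 × 0.05 = 2.10, and 65 × 2.10 = 136.5, against the stated 136.
- Dropout: 136 / 0.75 = 181.3, rounded up to 182.

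The chain reproduces with about 23 analysed patients in each of six teams per arm. The number of teams enters only through m.

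**Step 2: what the design effect restores.**
- m = 136/6 = 22.67
- DE = 1 + 21.67 × 0.05 = 2.083
- Effective n per arm = 136/2.083 = 65.28
- Standard error of the difference = √(2/65.28) = 0.175
- Noncentrality = 0.5/0.175 = 2.857

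**Step 3: power at that noncentrality, two-sided alpha 0.05.**

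| Reference distribution | Power |
|---|---|
| Normal | 0.815 |
| t, 270 df (patients counted) | 0.812 |
| t, 10 df (12 teams − 2) | 0.731 |
| t, 5 df (6 pairs − 1), no matching gain | 0.631 |

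A simulation of team means (200,000 replicates) gave 0.731 on 10 df and 0.630 on 5 df.

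**Step 4: detectable effect on 10 df.** Power of 0.80 needs a noncentrality of 3.11, so d = 3.11 × 0.175 = 0.54.

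**Step 5: paired analysis.** If matching removes a fraction r of the between-team variance, the variance of the contrast is 2 × [(1 − r) × 0.05 + 0.95/22.67]/6, tested on 5 df:

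| r removed by matching | Power |
|---|---|
| 0 | 0.63 |
| 20% | 0.68 |
| 40% | 0.73 |
| 50% | 0.76 |
| 60% | 0.79 |
| 80% | 0.86 |

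Power of 0.80 is reached at r of about 62%. The article gives no within-pair correlation, so no single row can be chosen.

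**Step 6: sensitivity.**
- ICC, at 136 per arm and 10 df: power 0.82 at ICC 0.03 and 0.55 at ICC 0.10.
- No dropout (182 analysed per arm): 0.78 on 10 df.
- Unequal team sizes: the article gives only an average size, so any spread is an assumption. With DE = 1 + [(1 + CV²) × m − 1] × 0.05, a CV of 0.3 to 0.5 gives about 0.71 to 0.68 on 10 df.

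**The case against.** The strongest reply is that nothing has been miscalculated. The sentence about 65 patients is true where it stands, before clustering is introduced; the design-effect formula is standard; and every number in the chain reproduces. All of that stands. The point is one of method, namely the step from an individually randomised power to a 12-team trial, and not an arithmetic slip.

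A second reply is that matching could recover the loss. Randomisation and blinding describes paired teams as alike in patients, catchment area and personnel, and Participants and setting spans very different age groups, diagnoses and settings. Much of the team-to-team variation may therefore lie between pairs. This is plausible, and it is why a reader should not infer that the design simply delivers 0.63, or a type II error of 37%. That figure needs both a 5-df paired analysis, to which the article does not commit, and no gain at all from matching. It does not rescue the 0.80 either, because the sample size calculation takes no credit for matching and gives no within-pair correlation.

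A third reply is that the ICC is itself a guess and matters more than the degrees of freedom. Step 6 bears this out, but 0.05 is the plan's own value, and the stated power should follow from it. Covariates or repeated measures might also add power; the calculation claims nothing for them.

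Finally, a reader might infer that a null result will be taken to rule out d = 0.5. The article does not say so, and that conclusion would rest on the final confidence interval rather than on planned power.

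**Conclusion.** The concern holds in this form: 0.80 is right for 65 individually randomised patients per arm, but it is not the power of the 12-team trial. On the plan's own inputs, with equal team sizes and a team-level contrast on 10 df, power for d = 0.5 is about 0.73. That is about 7 points below the stated value, or 8 points below the 0.81 that the plan's own inputs give when the number of teams is ignored. The corresponding type II error is about 27% rather than 20%, and the effect detectable with 80% power is about 0.54 rather than 0.50.

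The 10-df figure is the firm one, given ICC 0.05. The paired figure is a range that starts at 0.63 and depends on an unstated quantity. The effect of uneven team sizes rests on an assumed CV and is illustrative only.

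**What to change.** Keep the 364 patients and restate the power in the Sample size section. Suggested wording: *With 12 teams of equal size, 136 analysed patients per arm (22.7 per team), ICC 0.05 and two-sided alpha 0.05, the trial has about 73% power for d = 0.5 (t distribution, 10 degrees of freedom); the effect detectable with 80% power is about 0.54.*

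If a matched-pair analysis is intended, give its power only as a range that depends on the matching gain: 0.63 if matching removes none of the between-team variance, about 0.73 at 40%, and 0.80 at about 62%. Show how the figure moves with the ICC, and label any allowance for team-size variation as an assumption.

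The change is to text only. No patient, team, outcome or procedure is affected. The downside is a less favourable stated power.

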### Statistical analyses

The data will be analysed according to the intention-to-treat principle. In addition, a completer analysis will be performed. In order to assess whether randomization resulted in similar groups, differences between the two arms will be examined on relevant variables (e.g. sex, age, educational level, diagnosis, length of treatment, locus of control) using independent samples t-tests for the continuous variables and Chi-Square tests for the categorical variables. Variables that are distributed unevenly among the two arms will be entered as covariates when testing the effectiveness of the intervention. The hypotheses will be tested using multivariate linear regression and, due to the cluster randomisation, multi-level analyses.

In addition, the patients’ and clinicians’ views on the ROM-application (ROM questions), Shared Decision Making process (SDM-Q-9) and Working Alliance (WAI) will be compared. If they show different views, the interaction with the primary and secondary outcome parameters will be studied.

Analyses will be conducted using SPSS. Reporting of the results of the study will be in accordance with the CONSORT statement 2010 (extension cluster randomised trials).

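### Covariates for the effectiveness model are picked from the data by baseline significance tests that ignore team randomisation; a fixed set should replace the rule

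*Protocol article*

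**What the plan says.** The Statistical analyses section checks whether randomisation produced similar groups "using independent samples t-tests for the continuous variables and Chi-Square tests for the categorical variables". The variables are given only as examples: "e.g. sex, age, educational level, diagnosis, length of treatment, locus of control". The result then determines the model: "Variables that are distributed unevenly among the two arms will be entered as covariates when testing the effectiveness of the intervention". No threshold for uneven is given, and no covariate is fixed regardless of balance. The section on patients' characteristics at baseline treats these variables as possible covariates only.

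Clustering is recognised for the outcome but not for the baseline tests: "The hypotheses will be tested using multivariate linear regression and, due to the cluster randomisation, multi-level analyses". Under Trial design, "pairs of teams from the same mental health organisation are randomly assigned to either the experimental or control conditions (matched pairs". Under Participants and setting, "a total of six intervention and six control teams from four organisations participate".

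**The concern.** The rule is stated outright, so it is not a detail left to a fuller document. It has three weaknesses.

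- **The model depends on the data.** With an open list and no threshold, two analysts could reach different primary models from the same data, after arm-level differences have been seen.
- **The criterion is imbalance, not prognosis.** Adjustment gains precision when a covariate predicts decisional conflict. A predictor that happens to be balanced is left out, and an unrelated variable that happens to differ goes in.
- **The tests do not match the design.** They treat 364 patients as independent, although 12 teams were randomised in pairs. Where a baseline variable clusters by team beyond what pairing removes, the p-values are too small.

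At stake are the credibility of a prespecified primary analysis and some precision in a trial with six teams per arm.

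**Working it through.** **1. The plan's own figures.** The Sample size section says "This study is designed to detect a medium effect size of" d = 0.5, with α = 0.05 and 65 per arm for power 0.80. The exact two-sided t-test gives 0.808 at 65 per arm. With m = 136/6 = 22.67 analysed per team and ICC 0.05, the design effect is 1 + 21.67 × 0.05 = 2.083, and 65 × 2.083 = 135.4, so 136. Then 136/0.75 = 181.3, so 182 per arm, and 182/6 = 30.3 enrolled per team. The figures reproduce, and this point does not affect them.

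**2. False-flag rate of the baseline tests.** Inputs: m = 30.33 enrolled per team, from the article. Assumptions: a 5% two-sided cut-off (the article gives no threshold), the covariate ICC (the article's 0.05 is for the outcome), and the share s of between-team variance that is common to a pair and so cancels between arms. The true variance of the arm difference, relative to what the unadjusted test assumes, is approximately

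V = (1 − ICC) + m × ICC × (1 − s),

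and the flag rate is 2 × (1 − Φ(1.96/√V)). With s = 0, V is the usual design effect.

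At ICC 0.05:

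| s | V | 1.96/√V | flag rate |
|---|---|---|---|
| 0 | 0.95 + 1.517 = 2.467 | 1.248 | 21.2% |
| 0.5 | 0.95 + 0.758 = 1.708 | 1.500 | 13.4% |
| 0.8 | 0.95 + 0.303 = 1.253 | 1.751 | 8.0% |
| 1 | 0.95 | 2.011 | 4.4% |

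A simulation of six pairs with 30 per team (20,000 runs) gave 21.1%, 13.6% and 8.1% for the first three rows.

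Range over the assumed ICC:

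| ICC | s = 0 | s = 0.5 | s = 0.8 | s = 1 |
|---|---|---|---|---|
| 0.01 | 8.5% | 6.7% | 5.6% | 4.9% |
| 0.10 | 32.3% | 20.7% | 11.0% | 3.9% |
| 0.20 | 45.4% | 31.7% | 16.7% | 2.8% |

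A paired t-test on team means, which follows the design, stayed at about 5% in every simulated scenario.

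**3. Effect on the primary test.** An illustrative simulation used 23 patients per team, outcome and covariate ICC 0.05, and six covariates, two of them prognostic with assumed coefficients 0.4 and 0.3. The analysis was an unpaired team-level test, standing in for the multi-level model (3,000 runs per setting).

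| Adjustment | Type I error | Power at d = 0.5 | SD of estimate at d = 0.5 |
|---|---|---|---|
| None | 0.049 | 0.738 | 0.176 |
| Selected by imbalance | 0.042 | 0.775 | 0.162 |
| All six, fixed | 0.059 | 0.865 | 0.154 |

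The Monte Carlo error of the type I figures is about √(0.05 × 0.95/3,000) = 0.004. Further runs that varied the covariate ICC and the pairing gave type I error of about 0.02 to 0.05 under selection, with power of about 0.67 to 0.75 against 0.82 to 0.84 for the fixed set. The effect estimate under selection was unbiased (0.50 for a true 0.50).

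The fixed set's type I error of 0.059 in this simple two-stage analysis flatters its power slightly. The SDs are the cleaner comparison: 0.162/0.154 = 1.05, so the selected-covariate estimate is about 5% less precise.

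**The case against.** The strongest defence is that the hypothesis tests are multi-level, so clustering is handled where inference is made. A reader might infer that the two-step procedure makes the primary type I error and confidence interval invalid. The documents do not support that: nothing in the plan leads to it, and in simulation the error rate under selection was at or slightly below nominal, with no bias. This part of the defence stands.

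A reader might also take 21%, or 45% at ICC 0.20, as this trial's flag rate, and multiply up to a 76% chance of at least one false flag among six independent variables (1 − 0.788⁶). Those figures assume that pairing does nothing. The article describes the paired teams as alike in patients, catchment area and personnel. Clustering that arises because teams serve different age or diagnostic groups is largely shared within a pair and cancels between arms. With half of the variance shared at ICC 0.05, the six-variable figure is 58%; with 80% shared it is 39%. If all is shared, the tests fall slightly below 5%. This objection stands too.

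Nor can it be said that the rule picks the wrong variables as a matter of course. A flagged variable may be prognostic, the article does not say which variables predict decisional conflict, and imbalance-selected adjustment did better than none (0.775 against 0.738). A false flag only adds a covariate, which is what a fixed set does every time.

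Finally, clinicians recruit patients after teams are allocated, so real imbalance is possible and worth looking for. A descriptive table by arm and team shows it without a significance test deciding the model.

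None of this answers the first two weaknesses, which depend on no ICC: the model is not fixed in advance, and its covariates are chosen for imbalance.

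**Conclusion.** The point holds as a fault of prespecification and efficiency. The covariates of the effectiveness model are left to patient-level baseline tests on an open list, with no threshold and no regard to team-level, pair-matched randomisation.

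At an assumed covariate ICC of 0.05, the tests flag chance imbalance somewhere between 4% and 21% of the time, depending on how well the pairing works. The primary type I error is not inflated, provided the outcome test respects teams as the plan intends. The precision lost is illustrative only, since it rests on assumed prognostic coefficients: power of about 0.67 to 0.78 with selected covariates against 0.82 to 0.87 with a fixed set. The planned power of 0.80 does not rely on covariates, so the sample size is unaffected.

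This should be fixed, but it does not threaten the validity of the trial.

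**What to change.** - Delete the baseline significance tests and the rule that enters unevenly distributed variables.
- Before arm-level data are examined, fix the adjustment set of the multi-level model as matched pair, age, sex, educational level, diagnosis and length of treatment. Include them whatever the observed balance, and use the same set for all outcomes.
- Describe baseline characteristics by arm and by team, without p-values.
- Leave self-reported locus of control out of the main set and state why. The data collection procedures send the study questionnaires after the SDM-ROM conversation, so the T0 value in the intervention arm may already reflect the intervention.

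**Cost.** Two sentences of analysis text and no new data, since all five patient variables are already collected (Table 4) and the pairs are known. There are two small drawbacks. Entering matched pair uses five of the ten team-level degrees of freedom (12 − 2 = 10; six pairs take 6 − 1 = 5), which is the price of respecting how the teams were randomised. Pair will also overlap to some extent with age and diagnosis where teams are organised by patient group; this may make those coefficients imprecise, but they are not the quantity of interest.
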